Functional impairment of the upper limb due to other pathologies than strokeMedical conditions incompatible with research participation: uncontrolled medical illnesses (hypertension or diabetes, ischaemic heart disease, congestive heart failure, bronchial asthma, severe/untreated depression, agitation, end-stage renal/liver/heart/lung failure, unresolved cancers)Anticipated life expectancy of less than six monthsPacemakers and other active implantsActive seizures within three monthsLocal factors potentially worsened by intensive technology-aided upper-limb therapy and computer-based training:Spasticity - modified Ashworth Scale (MAS) [31] > 2 of any upper limb muscle groupsSevere pain in affected arm - Visual Analogue Scale for pain (pVAS) [32] > 5/10Skin woundsSevere visual impairment or visual neglect affecting the ability to use technologiesHistory of dementia, depression, or behavioural problemsPregnant or lactating females

After recruitment, participants may be withdrawn from the study in the following circumstances:

Poor fit to the technologies that could potentially cause complications (e.g., strain)Safety concerns (e.g., dizziness due to screen use)Serious adverse events related to the technologyNew medical problems unrelated to study intervention: recurrent stroke, new organ failure, new diagnoses rendering subject ineligibleNot complying with the study procedures

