#### Clinical scales.

The clinical upper limb status of the participants will be determined at every time point (t0 to t4) with standardized clinical scales for motor impairment (FMA and Grip strength (GS) measured by a digital dynamometer), functional performance (Action Research Arm Test (ARAT) [48], Box-and-Block Test (BBT) [49]), spasticity of the shoulder adductors, elbow, wrist, and finger flexors (MAS), and pain (pVAS).

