To evaluate the clinical impact of the TARGeT program, a two-way repeated measures analysis of variance (ANOVA) will be conducted for each clinical scale *time point* and *intervention group* as factors. The *time point* factor (pre, mid, post, follow-up 1, follow-up 2) is intended to assess both the immediate effects of the intervention and the long-term retention of the treatment gains. We hypothesize that motor function as assessed by ARAT etc. will improve significantly during the intervention period and that these gains will be maintained at follow-up. The *intervention group* factor (TARGeT intervention, conventional therapy) will compare the effects of the TARGeT intervention on clinical scales with duration-matched conventional therapy data from previous studies and the literature [9]. In addition, the interaction between *time point* and *intervention group* will be examined to determine whether temporal changes differ between groups. We hypothesize that the clinical impact (FMA, etc.) of the TARGeT program will be comparable to that of conventional therapy, validating the program as an effective technological alternative to traditional rehabilitative methods. Any additional health benefit in terms of quality of life will be determined by descriptive analysis of the SS-QoL and EQ-5D scales. Note that if the data violates the assumptions for parametric testing (normality – Shapiro-Wilk test, homogeneity of variance – Levene’s test), we will instead utilize the non-parametric test for these comparisons (e.g., Aligned Rank Transform ANOVA).

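### For single-muscle MAS and for pVAS, the fallback named as an example (Aligned Rank Transform ANOVA) inflates the group-by-time false-positive rate if about half or more of the scores share one value

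*Protocol article*

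**What the plan says.** In the Data analysis section of the protocol article, "a two-way repeated measures analysis of variance (ANOVA) will be conducted for each clinical scale". The time factor has five levels ("pre, mid, post, follow-up 1, follow-up 2"). The group factor ("TARGeT intervention, conventional therapy) will compare the effects of the TARGeT intervention on clinical scales with duration-matched conventional therapy data") draws on earlier studies and the literature. The interaction of the two "will be examined to determine whether temporal changes differ between groups".

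The switch is conditional: "if the data violates the assumptions for parametric testing", checked by Shapiro-Wilk and Levene, then "we will instead utilize the non-parametric test for these comparisons (e.g., Aligned Rank Transform ANOVA"). No other non-parametric method is named, and the sentence exempts no scale.

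The Clinical scales section puts "spasticity of the shoulder adductors, elbow, wrist, and finger flexors (MAS), and pain (pVAS") among the measures taken at t0 to t4. It does not say whether MAS is analysed per muscle group or summed. The exclusion criteria (Study design, setting and participants) remove people with "modified Ashworth Scale (MAS) [31] > 2 of any upper limb muscle" groups and those with a pain score above 5 out of 10.

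**The concern.** MAS for one muscle group has about four possible grades at entry (0, 1, 1+, 2 on the usual grading), and pVAS is confined to the lower half of its range. Such data are not normal, so the normality check will pass them to the fallback almost automatically.

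ART subtracts estimated means before it ranks. On a scale with many ties, this gives identical raw scores different aligned values depending on their cell, and ranking turns those chance differences into ordered blocks. The rule would then replace a test that holds its level on these data with one that does not. What is at stake is a spurious difference between the TARGeT cohort and the conventional-therapy data in the course of spasticity or pain.

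**Working it through.** **Inputs from the protocol article.** Two groups, five visits, target sample 25 in the TARGeT group, entry limits MAS 2 and pVAS 5. The article states no significance level, false-positive rate, comparator size or score distribution, so there is no figure of its own to reproduce.

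**Assumed.** Two-sided 0.05; 25 comparators (15 and 40 also tried) with individual, complete data at all five visits; one within-person correlation of 0.6 to 0.8 between all visits; the score distributions listed below; no true time or interaction effect.

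**Why ties matter.** For the interaction, ART ranks

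aligned score = score − group mean − visit mean + grand mean.

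With 2 × 25 × 5 = 250 scores and 60% zeros there are 150 zeros, about 15 in each of the 10 cells. On the raw scale all 150 tie at mid-rank (1 + 150)/2 = 75.5. After alignment, a zero takes a value set only by its cell's group and visit means, so the zeros split into up to ten blocks. If the means differ by less than one grade, the blocks still fill ranks 1 to 150, with mid-ranks 8, 23, 38, …, 143. A chance difference in means far smaller than one grade becomes a shift of 15 to 135 ranks shared by every zero in the cell. Ranking does not preserve additivity, so part of this appears as interaction.

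**Routing.** Shapiro-Wilk at 0.05 on residuals rejected in 100% of simulated data sets for every four-grade single-muscle MAS and every pVAS distribution tried, and in 99.5-100% for a MAS summed over four muscle groups.

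**False-positive rate for the interaction**, 25 per group, 1,500 to 2,000 runs per setting. The Monte Carlo standard error at 5% is √(0.05 × 0.95/2000) = 0.5 points, or 0.6 with 1,500 runs.

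| Scores | ART |
|---|---|
| MAS, one muscle, spread out (even, or 40% at zero) | 6-10% |
| MAS, 50% at zero | 12-13% |
| MAS, 60% at zero | 13-18% |
| MAS, 70% at zero | 20-24% |
| MAS, 75% at zero | 22-26% |
| pVAS in whole numbers, 50% at zero | 11% |
| pVAS in whole numbers, 65% at zero | 16-20% |
| pVAS in whole numbers, 80% at zero | 28-32% |
| pVAS in 0.1 steps, 30 / 50 / 70% at zero | 6 / 11 / 21% |
| MAS summed over four muscle groups | 5-8% |
| FMA-like and ARAT-like | 4-6% |

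The ordinary ANOVA on the same data gave 3.3-6.8% across the null effects tested.

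**Unequal groups (correlation 0.7).** With 15 comparators against 25, ART gave 13% (MAS, 40% zeros), 20% (MAS, 60%) and 35% (pVAS, 80%). With 40 against 25 it gave 26% (MAS, 60%) and 45% (pVAS, 80%).

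**Cohorts differing in level by 0.5 SD, 25 per group.** The interaction rate was 7% (MAS, 40% zeros), 15% (MAS, 60%) and 24% (pVAS, 65%).

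**Main effects under ART.** With equal group sizes and levels, time gave 5-13%. It reached 29% with unequal sizes and 21% with the 0.5 SD level difference. The group effect gave 5-16%.

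**The case against.** Several points on the other side stand.

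- ART is introduced only as an example, and the choice of test for each scale may be settled in an analysis plan that is not shown. A reader might infer that MAS and pVAS are bound to be tested by ART. The text supports only that they will reach a non-parametric fallback for which ART is the one method named.
- The entry limits cap the top of each scale, and only at entry. They do not show that half the scores will be zero. A reader might take 11-30% as a property of these scales, but it is conditional on a floor share that the article does not give.
- If MAS is summed over muscle groups, there is almost no inflation.
- The interaction can be tested only if comparator MAS or pVAS data exist for individuals at all five visits, which cannot be seen from the article.
- A reader might infer that the named hypotheses are undermined. They concern ARAT and FMA, and ART holds its level on such many-valued scales.
- A reader might also infer that a false positive would decide the safety conclusion. The Follow-up phase section does list pVAS and MAS under adverse-event monitoring. However, the Journal and report forms and Data analysis sections base safety on reported concerns and interviews, not on this ANOVA.
- Clinical scales are secondary outcomes, and the Discussion already asks for caution on effectiveness.

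These points limit the reach of the concern without removing it. The only method named is unsuitable for two scales likely to reach it if their scores are concentrated, and nothing in the text keeps it away from them.

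**Conclusion.** The concern holds in a conditional form. A single-muscle MAS or a pVAS will almost always fail Shapiro-Wilk. If about half or more of the scores share one value, ART raises the group-by-time false-positive rate from 5% to about 11-30% with 25 per group, and to as much as 45% in the unequal-group settings tried. With spread-out scores it is about 6-10%. Time effects are inflated less when the groups are alike in size and level. The ordinary ANOVA that the rule would displace stays near 5%.

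The size rests on the assumed floor share, comparator data and correlation. The simulations used one correlation for all visit pairs and no missing data, so they do not show how either method behaves otherwise. The matter affects two secondary scales. It is worth correcting because the change is small and the error reproducible.

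**What to change.** State in the Data analysis section that ART will not be used for MAS and pVAS, and say whether MAS is analysed per muscle group or summed. For these two scales, do one of the following:

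1. keep the repeated-measures ANOVA regardless of the normality test; or
2. for any between-group comparison, use a permutation test on the t0-t2 change.

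In either case report, per visit, how many TARGeT participants are better, unchanged and worse than at t0 (by muscle group for MAS), with an exact sign or signed-rank test for t0-t2.

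The cost is analysis wording only; no data collection changes. The second option gives up the omnibus interaction test for these two scales. Neither option makes the comparison with external data a randomised one.

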### Status and timeline of the study

Data collection started on 12 August 2024 prior to publication of this manuscript and continues until 05 June 2026. Complete analyses will be performed after the completion of data collection and the results will be shared after data analyses are finalized.

## Discussion

This protocol paper outlines a proof-of-concept and feasibility study designed to evaluate the potential of a unique home-based, multi-technology therapy concept for unsupervised technology-assisted upper-limb rehabilitation in stroke survivors. The proposed TARGeT program aims to address key challenges in current stroke neurorehabilitation, including limited access to therapy, high costs, and the difficulty of maintaining functional gains in the outpatient phase. This study will assess this therapy model’s feasibility, safety, and user experience and aims to provide preliminary insights into its potential clinical impact and economic benefits.

Despite the growing use of rehabilitation technologies in clinical settings and the advocated benefits of using technology to promote decentralized rehabilitation [16], to the best of our knowledge, this is the first study to advance home-based neurorehabilitation by offering a suite of actuated (robotic) and non-actuated technologies for unsupervised therapy directly in stroke survivors’ homes. This has the potential to address the increasing demand for neurorehabilitation while tackling the shortage in clinical manpower and reducing the traveling inconvenience by providing comprehensive, high-dose, home-based therapy. Enabling stroke survivors to perform unsupervised therapy at home allows them to train at their convenience, independent of scheduled therapy sessions at clinics or rehabilitation centers. This flexibility may enhance therapy compliance [17], increase the total therapy dose received [10,56], and improve patient satisfaction [57], while delivering clinical benefits comparable to in-clinic therapy [58,59]. This study harnesses the potential of home-based therapy by deploying complementary technologies that target both proximal and distal upper extremities and include somatosensory, motor as well as cognitive components. This unique combination provides flexibility to design a holistic therapy plan suitable for most stroke survivors, and that could efficiently address the complexity of upper limb (and in particular hand) sensorimotor function. It moreover allows to adjust the training more specifically to the changing needs along the rehabilitation journey of stroke survivors, just like in clinical practice. The technologies employed were all previously successfully tested individually, are scalable, and easy to use, such that we assume that they can be used at home in an unsupervised manner. To ensure high quality therapy at home, users will be trained on the operation of the devices in few onboarding sessions in the clinic and at home with the help of clinical personnel. In addition, therapists stay involved in the therapy by being available on demand and by remotely monitoring the training progress from the clinic. The outcomes of the study will inform on the feasibility, safety, usability and user experience and give insights into the clinical and economical comparability to conventional therapy. It will also pave the way for a future larger-scale TARGeT study to investigate the cost-effectiveness of such a novel home rehabilitation service.

Alongside the increased access to therapy, the fully unsupervised training at home has the potential to drastically reduce the demand for trained therapists. During the six weeks of daily high-intensity training at home, only two conventional therapy sessions in the clinic and five technology-onboarding sessions are scheduled. Additionally, therapists will remotely monitor the stroke survivors’ training progress via a dedicated web-based interface to ensure the quality and safety of the at-home therapy and get in contact in case of non-use of the technologies. Unlike in traditional therapy or in recent telerehabilitation trials [60,61], this progress check will be done asynchronously from the training times of the stroke survivors and, thus, gives therapists full flexibility to accommodate these checks to their schedule and downtimes, e.g., between clinic/home visits. The reduced number of clinic visits further reduces the travel expenses and burden on caregivers. On the other hand, our blended intervention approach ensures the therapy is tailored to the individual by integrating in-person and digital methods to best support the user at home and to optimize the functional gains.

By freeing up therapists’ time, this therapy model has the potential to directly decrease the direct costs of the service. Moreover, shifting the training location to the home environment lowers transportation costs. Not-scheduled, unsupervised therapy, furthermore, has the potential to reduce costs linked to productivity loss of the stroke survivor since it allows scheduling the training as per one’s convenience. Up until now, economic evaluations of technology-aided rehabilitation remain scarce [62], particularly in decentralized settings, yet such evaluations are crucial for assessing the real-world viability of these novel therapy concepts.

The comprehensive outcomes of this feasibility study will inform whether a statistically powered randomized controlled trial is feasible and necessary to fully assess the potential of the TARGeT concept. Therapists’ inputs on the technology order and the assigned therapy plans, linked with individual stroke survivor’s characteristics and performance data with the technologies, can potentially inform on the most suitable technology and exercise for a specific impairment status [16,63,64]. This can be a further step towards more autonomous therapy without supervision leading to potentially easier access to high-quality neurorehabilitation.

Despite its innovative design, this study has several limitations. First, as a proof-of-concept feasibility study without a randomized controlled design, conclusions regarding clinical effectiveness and comparability to conventional therapy will be limited and should be interpreted with caution. Second, adherence to unsupervised home-based training may vary substantially across participants and may be influenced by unmeasured factors such as motivation, or personal circumstances. And third, caregiver experience and perceived burden are not comprehensively assessed which may prevent capturing the full impact of such a therapy program.

In summary, this protocol sets the foundation for evaluating the feasibility, usability, and safety of an unsupervised, at-home multi-technology rehabilitation model. Findings from this study are expected to inform further development and refinement of the protocol and the technologies and may ultimately contribute to establishing technology-aided home rehabilitation as a viable complement to traditional therapy paradigms.
